### Analytic strategy

#### Analysis of power for primary effects

The target sample size for this study was based on achieving adequate power for the secondary analyses (since the primary analyses were proportions based on feasibility). The goal was to have 80% power at a significance level of .05, to test the efficacy of the online MBCR intervention in reducing mood disturbance, compared to the control group. On the basis of observed means and standard deviations in three F2F comparable trials [22,26,46]: the estimated effect sizes for group differences in pre- to post-intervention change on the POMS total mood disturbance score was 0.72, 0.51 and 0.58 respectively. Based on the three trials above, and following the more conservative estimation rule proposed by Dattalo (2008) [47] to use t-test estimations for RM-ANOVA designed studies, 26 participants are required for each group to detect a significant difference between the groups. Taking into account the likelihood of 20% attrition as observed in F2F MBSR trials, a total of 32 participants will be recruited for each group—a total sample size of 64 participants.

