### Data analysis

All data analysis will be carried out at the completion of the study using the most up-to-date version of SPSS for Windows. Tests will be performed with a two-sided alternative hypothesis, at a critical significance level of 5%. To ensure the appropriateness of the analysis the distributional normality of the data will be confirmed. Wherever possible, p-values and effects sizes will be reported.

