### Secondary objective – primary outcome

Total Mood Disturbance scores will be examined with a 2 (group) × 2 (time) RM-ANOVA to examine main effects of time and group, and any interactions between time and group. Post-hoc analyses will be conducted to examine the simple main effects for treatment if a significant interaction is detected.

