## Discussion

Recruitment for this trial has proceeded as anticipated; with participants arriving through the Alberta Cancer Registry via study invitation letters, through rural cancer centre posters, pamphlets, advertisements, and community-based networks. To date, 1800 individuals have been contacted through the Alberta Cancer Registry through mailed study invitation with 157 responding. Of those, 41 were ineligible (8 deceased, 3 outside of primary treatment inclusion criteria, 12 had scheduling conflicts, 9 had low distress, 6 had no computer/high speed Internet, 2 were living outside Alberta, and one individual was not diagnosed with cancer). 54 declined participation (with the majority stating they were not interested in the intervention, while 10 stated they were effectively managing stress through other methods. 5 asked to be contacted later or considered for the program at a later date. 57 participants have been enrolled thus far in the program: 2 withdrew (1 MBCR, 1 wait-list). Reasons for discontinuing with the study included treatment related issues and schedule change. 47 have completed the program or in the process of completing the study. No adverse events have been reported. Final analysis of the data is not yet available to compare the intervention and control groups; however, several preliminary comments and conclusions can be made from the experience of the trial to-date.

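### The fixed 2 × 2 RM-ANOVA is an unadjusted change-score comparison of participants with both T1 and T2, in a trial that plans for 20% attrition; a baseline-conditioned model is better and costs only wording

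*Protocol article*

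**What the plan says.** In the protocol article, the section Secondary objective – primary outcome specifies that Total Mood Disturbance (POMS) is analysed by a 2 (group) × 2 (time) "RM-ANOVA to examine main effects of time and group, and any interactions between time and group". The section Secondary objectives extends this to stress, mindfulness, spirituality and post-traumatic growth. Data analysis names SPSS.

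Analysis of power for primary effects states that "26 participants are required for each group to detect a significant difference between the groups". It continues: "Taking into account the likelihood of 20% attrition as observed in F2F MBSR trials", "a total of 32 participants will be recruited for each group", which gives 64 in all.

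The Discussion reports 57 enrolled and 2 withdrawn, one in each arm, and adds: "Reasons for discontinuing with the study included treatment related issues and schedule change". Procedures describes email and telephone reminders for unreturned questionnaires and makes no exception for people who stop attending classes.

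The article names no analysis set and no rule for a missing T2.

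**The concern.** The article names its model, so this is more than silence about missing data. In a 2 × 2 RM-ANOVA the group-by-time test compares mean change between arms. A participant without T2 has no change score, so the T1 already collected goes unused. The comparison also takes raw change and makes no adjustment for where each participant started.

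Two things are at stake. The first is bias. If people with high baseline distress are lost more often from one arm than from the other, the retained arms differ at baseline. Part of that difference then appears in the change contrast through regression to the mean. The arms ask for different things: MBCR requires weekly 2-hour classes, a full-day retreat and daily home practice, while the wait-list requires waiting for the course. Unequal loss is therefore plausible, though not shown. The second is precision, because raw change is a less efficient contrast than one conditioned on baseline, whether or not anyone is lost.

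**Working it through.** **1. The plan's own attrition step.** Inputs from the power section: 26 per group, 20% attrition, 32 recruited per group.
- 26 / (1 − 0.20) = 32.5, so 33 per group. 26 × 1.20 = 31.2, so 32 per group. The stated 32 follows from the second form and is within one participant per group of the first.
- At 20% loss, 32 × 0.80 = 25.6 per group have T2, about 51 of 64. The other 64 × 0.20 = 12.8, about 13, would not enter the RM-ANOVA.
- At the withdrawal rate reported so far, 2/57 = 3.5%, and 64 × 0.035 is about 2. Follow-up was incomplete at that point.

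I take the 26 as given. Whether it follows from the stated effect sizes is a separate question and does not affect this point.

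**2. Bias of the change contrast.** Let T1 and T2 have equal variance (SD = 1) and correlation r. If the retained members of one arm have mean baseline m, their expected T2 is shifted by r·m, so their mean change is shifted by −(1 − r)·m.

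The article gives no T1–T2 correlation for Total Mood Disturbance. I assume r = 0.65 to 0.74. These are the POMS retest values quoted for the vigor and depression subscales over about 20 days, so they stand in for the total score over 8 weeks.

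*Extreme case (assumed):* the 20% with the highest baseline are lost from MBCR only, and wait-list loss is random.
- Retained mean: m = −φ(0.8416)/0.80 = −0.280/0.80 = −0.35.
- Shift in change: 0.35 × 0.35 = 0.12 SD at r = 0.65; 0.26 × 0.35 = 0.09 SD at r = 0.74.
- Higher scores mean worse mood, so a positive shift makes MBCR look less effective.
- For scale, the three effect sizes in the article ("POMS total mood disturbance score was 0.72, 0.51 and 0.58 respectively") average 0.60 in change-SD units. In baseline-SD units this is 0.60 × √(2(1 − r)) = 0.50 at r = 0.65 and 0.43 at r = 0.74. The bias is then 0.1225/0.50 = 24% and 0.091/0.43 = 21% of it.

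*Milder case (assumed):* 20% lost from MBCR, with the odds of loss multiplied by 1.5 or 2 per baseline SD, and wait-list loss random.
- Numerical integration over a normal baseline gives m = −0.079 and −0.129.
- Bias: 0.021 to 0.028 SD for the factor 1.5, and 0.033 to 0.045 SD for the factor 2.

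*Extreme selection at 3.5% loss in one arm:* m = −0.0774/0.965 = −0.08, so the bias is 0.02 to 0.03 SD.

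**3. Precision.** The variance of the treatment contrast is proportional to 2(1 − r) for raw change and to 1 − r² when conditioned on baseline. The ratio is (1 + r)/2.
- r = 0.65: 0.825, a reduction of 17.5%.
- r = 0.74: 0.870, a reduction of 13%.

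This gain applies with or without missing data.

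**4. Where the remedy acts.** In a two-time-point model with a common baseline mean, the likelihood splits into a part for T1 and a part for T2 given T1 and arm. The treatment effect is estimated from the second part, so it equals the baseline-adjusted ANCOVA estimate among those with T2. Fitting both to one simulated data set gave the same estimate. The bias in step 2 is therefore removed by conditioning on baseline, provided T2 is missing at random given T1 and arm. Participants with T1 only enter the model but add no information on the treatment effect.

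**The case against.** The strongest reply is that the article declares no completer analysis, and that an analysis set and missing-data rule belong in a fuller protocol or analysis plan that is not shown. This stands in part. A reader might infer that the trial has committed itself to a completers-only efficacy result, and the documents do not support that. RM-ANOVA requires a T2 score and not course completion, so someone who leaves the classes but returns T2 stays in. The reminder procedure already covers such people. Imputation before the RM-ANOVA is not ruled out either. What the reply does not reach is the named model: even with every T2 present, it is an unadjusted change comparison.

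A reader might also take the 20% allowance as an error. It is ordinary planning and does not define who is analysed.

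The size of the bias is open to challenge as well. The extreme case assumes perfectly selective loss in one arm. Only two withdrawals are reported, one per arm, and one of the two kinds of reason listed is a schedule change. That is fair, and the milder figures are the more realistic guide.

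Finally, a complete-case ANCOVA would remove the same bias. That is correct, but it is an argument for conditioning on baseline and does not defend the RM-ANOVA. Efficacy is also the secondary objective, which limits the stakes.

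**Conclusion.** The point holds in a limited form. The article fixes, for mood and the other patient-reported outcomes, a test that cannot use anyone without T2 and does not condition on baseline, while the sample size allows for losing about 13 of 64.

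The bias is conditional: it arises only if T2 loss depends on baseline distress and differs by arm. It is 0.09 to 0.12 SD in a deliberately extreme case, about 0.02 to 0.045 SD under milder selection at 20% loss, and smaller still if loss stays near 2 of 57. All these figures rest on r borrowed from subscale retest values. In these scenarios the bias hides benefit, so they give no support to a reading that the plan would exaggerate the effect. The loss of precision, 13 to 18% of variance at the same r, does not depend on dropout and is the firmer part of the case. The change is worth making because it is cheap and, according to the Discussion, the comparison of the arms was not yet available.

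**What to change.** In Secondary objective – primary outcome, replace the RM-ANOVA as the main efficacy analysis with a linear mixed model (SPSS MIXED) on T1 and T2 with a common baseline mean. Include all randomised participants as allocated. A baseline-adjusted ANCOVA among those with T2 gives the same treatment estimate and is an acceptable equivalent. Apply the same model to the outcomes under Secondary objectives.

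Add one sensitivity analysis in which MBCR participants missing T2 are assumed to gain no benefit. With 20% of that arm missing, this multiplies the estimated effect by about 0.8. Keep the RM-ANOVA as a supportive analysis.

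The sample size paragraph needs no change on this account, and the reminder procedure already applies to people who stop attending. The cost is wording, a missing-at-random assumption to be stated openly, and one extra run. No new data or staff are needed.

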### Data analysis

All data analysis will be carried out at the completion of the study using the most up-to-date version of SPSS for Windows. Tests will be performed with a two-sided alternative hypothesis, at a critical significance level of 5%. To ensure the appropriateness of the analysis the distributional normality of the data will be confirmed. Wherever possible, p-values and effects sizes will be reported.

### Demographic variables

Participants will be compared using t-tests or chi-square analyses (as appropriate) on primary demographic and psychological variables at baseline to ensure randomization success.

### Primary objective – feasibility

Feasibility will be assessed at the completion of the study through the following measures: 1) Proportion “interested”: this is difficult to ascertain as our reach is hard to know (i.e. the denominator), but we will use the number of invitation letters sent out through the Alberta Cancer Registry as a proxy denominator. The number of patients who phone in with interest in the study will be the numerator (target: 5%). 2) Proportion “eligible”: the number who meet eligibility criteria, over the number who called in (target: 30% - this number is low primarily due to the distress score greater than or equal to 4/10 inclusion criteria). 3) Proportion “consented”: the number of those who consented to the study over the total number who were eligible (target: 85%). Reasons for non-consent will be captured where possible. 4) Proportion “completed”: the number who completed the online intervention, over the number who consented (Target: 85%). Reasons for non-completion will be captured. The study will be deemed feasible if we are within 5% of each target value. Program satisfaction will be assessed through an evaluation form created for the study which assesses participants’ experiences of the MBCR program, the online group, and with the technology.

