### Recruitment

Potentially eligible participants in Alberta are identified through media outreach, promotional pamphlets, community based networks, and by cancer registry case records to mail study invitation letters. In Alberta, only one major cancer centre has MBSR classes specifically for individuals diagnosed with cancer; therefore all individuals who are unable to attend these F2F classes would be eligible to participate. The Alberta Cancer Registry estimates as of September 2011, 25,000 individuals diagnosed with cancer are eligible to be contacted for the trial. According to research conducted by the PI, approximately 35-45% of these individuals will meet criteria of being distressed. Additionally, 77% of Albertans 16 years of age and older have Internet access and 429 communities throughout the province of Alberta have broadband Internet (http://www.albertacanada.com; http://www.albertasupernet.ca). This forms a potentially large cohort to identify individuals living with cancer who have Internet access for this study.

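### The 'interested' feasibility measure counts callers from any source but divides by registry letters only, so each non-letter caller counted lifts it above the letter response rate

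*Protocol article*

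**What the plan says.** In the Protocol article, section Primary objective – feasibility, the first of four proportions is built as follows.

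- Denominator: "we will use the number of invitation letters sent out through the Alberta Cancer Registry as a proxy denominator". The reason given is that "this is difficult to ascertain as our reach is hard to know (i.e. the denominator".
- Numerator: "The number of patients who phone in with interest in the study will be the numerator (target: 5" percent is the target that follows. No limit by source of referral is attached.
- Decision rule for all four proportions: "The study will be deemed feasible if we are within 5% of each target value".

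The Recruitment section says that potential participants are "identified through media outreach, promotional pamphlets, community based networks, and by cancer registry case records to mail study invitation letters". The Discussion confirms that, besides registry letters, participants have arrived "through rural cancer centre posters, pamphlets, advertisements, and community-based networks". On progress it reports that "1800 individuals have been contacted through the Alberta Cancer Registry through mailed study invitation with 157 responding", and then breaks those responders down.

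**The concern.** A proportion needs a numerator drawn from its denominator. Here the denominator is the set of letters sent, while the numerator, read as written, is everyone who calls. Someone who saw a poster and phones in adds one to the top and nothing to the bottom. The ratio then no longer estimates how many letter recipients are interested. Nor does it estimate interest among everyone reached, because true reach is larger than the number of letters.

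What is at stake is one of the four criteria by which the primary objective is judged. Two studies with the same willingness among letter recipients could report different values because one advertised more.

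**Working it through.** **Inputs, all from the Protocol article.** Target 5% and the 'within 5%' rule (Primary objective – feasibility). Letters sent to date 1,800; responders 157; ineligible 41; declined 54; asked to be contacted later 5; enrolled 57 (Discussion). No count of callers by channel is given anywhere.

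**1. Reproduce the interim figures.**
- Reasons for ineligibility: 8 + 3 + 12 + 9 + 6 + 2 + 1 = 41, as stated.
- Responders: 41 + 54 + 5 + 57 = 157, as stated.
- Responders over letters: 157/1800 = 8.72%.

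**2. Form of the measure.** Let L be letters sent, m the letter recipients who call, and k the callers from other channels.
- Matched rate: m/L.
- Rate as written: (m + k)/L = (m/L) × (1 + k/m).

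The relative excess over the letter response rate is k/m. It is positive as soon as k is at least 1, and the ratio has no ceiling at 100%. Sending more letters shrinks the effect of a single caller (1/L), but not the relative excess if the mix of callers stays the same.

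**3. If the 157 already include other channels.** Let s be the share of the 157 that came by other routes (an assumption). The matched rate is 157 × (1 − s)/1800.

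| Assumed s | Matched rate |
|---|---|
| 0% | 8.7% |
| 10% | 7.9% |
| 25% | 6.5% |
| 50% | 4.4% |

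**4. If the 157 are letter responders only.** The matched rate is 8.7%, and the written definition gives (157 + k)/1800 for an assumed k.

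| Assumed k | Rate as written |
|---|---|
| 10 | 9.3% |
| 50 | 11.5% |
| 100 | 14.3% |

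**5. Which case applies.** The sum in step 1 places all 57 enrolled participants among those who responded to the letters. The same section says that participants also arrived by other routes. Either some of the 157 are not letter responders, or participants from other routes are left out of the 57. The text does not settle this.

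**6. Effect on the decision rule.** The document does not say whether 'within 5%' means percentage points or a relative margin.
- Percentage points: the band is 0% to 10%. Starting from 8.7%, extra callers move the figure towards failing.
- Relative: the band is 4.75% to 5.25%. The figure of 8.7% is already outside it.

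**The case against.** The limitation is partly disclosed: the authors say that reach is hard to know and call the denominator a proxy. The numerator is also defined straight after the registry letters are named, so a letter-only reading is possible. The one application shown looks matched, since the Discussion ties the 157 to mailed invitations. On this view the point is a small wording clarification.

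Much of this stands. A reader might infer that the interim 8.7% is inflated, or that the interim report mixes channels. The documents do not support either: the breakdown summing to 157 fits equally well with all 157 being letter responders. Nor do they show that the measure mainly reflects advertising effort, because no number of non-letter callers is reported.

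What does not stand is that the word 'proxy' cures the definition. It concedes an imperfect denominator and leaves the numerator unmatched to it. A matched ratio was available from the same letters. The rule is to be applied at completion, and nothing in the text tells the analyst to leave out callers from other routes.

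**Conclusion.** The concern holds as a fault in the stated definition. Followed as written, the 'interested' figure exceeds the letter response rate whenever a caller from another channel is counted. The direction is certain. The size is not known, because it depends on counts by channel that the document does not give. Under the assumption that 10% to 50% of the 157 came by other routes, the matched interim rate would be 7.9% to 4.4%; if none did, it is 8.7%.

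Two stronger readings should be left aside.

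- A reader might subtract the 8 deceased and all 54 who declined, get 95/1800 = 5.3%, and set that against 8.7%. The Discussion never calls the 157 the 'interested' numerator. Only a majority of the 54 are said to have been uninterested, and some may have called with interest and declined later.
- A reader might say that 24 non-letter callers break the criterion, since (157 + 24)/1800 = 10.06%. That assumes a percentage-point band, 1,800 letters and 157 letter-only responders, and the document fixes neither the first nor the last. It would also be a failure by excess, not a flattering result.

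**What to change.** Limit this criterion to registry letters:

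- **Numerator:** letter recipients who call with interest in taking part.
- **Denominator:** letters sent, less those known to have gone to deceased patients or to have been undelivered.
- **Other channels:** record the source at first contact, and report callers from other routes separately as counts, outside the proportion.

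The second measure, eligible over all who called in, can keep callers from every source, because eligible callers are a subset of callers. The text should then say that the two measures use different sets of callers.

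In the final report, state how many of the 157 responders and 57 enrolled came from letters, as far as the source can still be established.

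The cost is one field in the call log and one sentence in the definition, and the reported interest rate may be lower. The article says that recruitment was to continue through April 2013, with feasibility assessed at completion, so at the time of writing the change could still be made before the criterion is applied.

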### Secondary objective – primary outcome

Total Mood Disturbance scores will be examined with a 2 (group) × 2 (time) RM-ANOVA to examine main effects of time and group, and any interactions between time and group. Post-hoc analyses will be conducted to examine the simple main effects for treatment if a significant interaction is detected.

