### Primary outcome measure

#### Profile of Mood States (POMS)

The POMS is an instrument with 65 items that assesses six affective dimensions and produces a Total Mood Disturbance (TMD) score [41]. Psychosocial interventions (including psychological adaptation to diagnosis and treatment of cancer) frequently use this scale. This instrument measures state (vs. trait) attributes, therefore the POMS scale is an appropriate instrument for repeated measures as previous administrations do not influence later administrations. The Kuder-Richardson overall internal consistency measure of the six subscales ranged from 0.84 (Confusion) to 0.95 (Depression) in two separate studies, with test retest stability ranging from 0.65 (vigor) to 0.74 (depression) over approximately a 20 day period. This is consistent with this particular instrument as a measure of mood states, which are expected to vary over time, and supports its construct validity.

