### Secondary objectives

Secondary Outcomes: The same analytic strategy will be applied to the secondary outcomes of symptoms of stress, mindfulness, spirituality and posttraumatic growth.

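### The 2 × 2 RM-ANOVA for efficacy is valid but generally less precise than an ANCOVA on the baseline score that the trial already collects

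*Protocol article*

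**What the plan says.** All references are to the protocol article.

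- **Secondary objective – primary outcome:** the POMS total is analysed by a two-group, two-time "RM-ANOVA to examine main effects of time and group, and any interactions between time and group". Simple effects are followed up only if the interaction is significant.
- **Secondary objectives:** "The same analytic strategy will be applied to the secondary outcomes of symptoms of stress, mindfulness, spirituality and posttraumatic growth".
- **Study design; Procedures; Treatment as Usual:** the between-arm comparison has one assessment before (T1) and one after (T2) the programme or the wait.
- **Screening, consent and enrollment:** the questionnaire package is given before allocation, so T1 is a pre-randomisation measurement.
- **Data analysis:** tests are two-sided at 5%, run in SPSS at study completion.
- **Analysis of power for primary effects:** "The goal was to have 80% power at a significance level of .05". The inputs are three between-group effects on POMS change (0.72, 0.51, 0.58), and the result is 26 per group.
- **Profile of Mood States (POMS):** "test retest stability ranging from 0.65 (vigor) to 0.74 (depression"), over roughly 20 days.
- **Demographic variables:** arms are compared at baseline with t-tests or chi-square tests "to ensure randomization success".

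No baseline covariate is named for any efficacy analysis.

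**The concern.** With two time points, the group-by-time F statistic is the square of the two-sample t on T2 minus T1. A change score subtracts the whole baseline value, as if the slope of T2 on T1 were 1. When the slope is below 1, this over-corrects: baseline noise enters the estimate, and a chance difference between arms at T1 carries into the treatment effect with the opposite sign. ANCOVA estimates the slope from the data and avoids both.

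At stake is precision on the outcome that sets the size of the whole trial, in a small sample where baseline gaps between arms are likely. The adjusting variable is already being collected, so the precision would be given up for no saving.

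**Working it through.** **1. The plan's own figure.** A two-sided two-sample t-test at 5% with 80% power needs 32, 48 and 62 per group at effects of 0.72, 0.58 and 0.51. The stated 26 is not reproduced. That is a separate matter; 26 is used below only as the number per arm that the plan expects to analyse.

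**2. Inputs and assumptions.**
- n = 26 per arm, two-sided 5% (from the article).
- Effect d = (0.72 + 0.51 + 0.58)/3 = 0.603, in units of the SD of change. This mean is illustrative; the article does not plan on it.
- Pre-post correlation r = 0.65 to 0.74. These are subscale retest figures over about 20 days. The 8-week correlation of the total score is not given, so r = 0.5 is shown as well.
- k = SD(T2)/SD(T1). The article does not give it. k = 1 is the base case.

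**3. Variance ratio.** With T1 variance 1:

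Var(ANCOVA)/Var(change) = k²(1 − r²)/(1 + k² − 2rk), which is (1 + r)/2 when k = 1.

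| r | k = 1 | Equivalent n per arm, 26/ratio | k = 1.2 |
|---|---|---|---|
| 0.50 | 0.75 | 34.7 | 1.44 × 0.75/1.24 = 0.871 |
| 0.65 | 0.825 | 31.5 | 1.44 × 0.5775/0.88 = 0.945 |
| 0.74 | 0.87 | 29.9 | 1.44 × 0.4524/0.664 = 0.981 |

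A smaller T2 SD moves the ratio the other way. At k = 0.9 and r = 0.65 it is 0.81 × 0.5775/0.64 = 0.731.

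**4. Power at 26 per arm, d = 0.603.** The change-score test has 56.9% (noncentral t). Dividing d by the square root of the ratio gives large-sample ANCOVA figures of 69.3%, 65.1% and 62.8% at r = 0.5, 0.65 and 0.74 with k = 1. These ignore the cost of estimating the slope. Simulation (40,000 runs per setting) includes it:

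| r | ANCOVA, k = 1 | ANCOVA, k = 1.2 |
|---|---|---|
| 0.50 | 68% | 62% |
| 0.65 | 64% | 58% |
| 0.74 | 62% | 57% |

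The change-score test stayed at about 57% throughout.

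**5. The cited effects one by one (k = 1, large-sample).**

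| d | Change score | ANCOVA, r = 0.74 | ANCOVA, r = 0.65 | ANCOVA, r = 0.5 |
|---|---|---|---|---|
| 0.72 | 72.1% | 77.9% | 80.0% | 83.6% |
| 0.58 | 53.6% | 59.4% | 61.7% | 65.8% |
| 0.51 | 43.8% | 48.9% | 51.0% | 54.9% |

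**6. Chance imbalance.** The SD of the T1 difference between arms is √(2/26) = 0.28 SD, so a gap above 0.2 SD in either direction occurs in about 47% of such trials. Given a gap of 0.28 SD and r = 0.65, the change-score estimate shifts by (1 − 0.65) × 0.28 ≈ 0.10 SD. The illustrative effect in the same units is 0.603 × √(2 × 0.35) = 0.50 SD, so the shift is about 19% of it. A baseline t-test on such a gap gives p of about 0.3 and would raise no flag.

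**The case against.** The strongest reply is that nothing here is an error. The hypotheses concern greater change in the treated arm, the sample size is built on effects on change, and the interaction tests exactly that. Under randomisation it is unbiased with the right type I error. All of this stands, and it limits the point to efficiency.

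The size of the gain is also uncertain. The correlation is a proxy, and equal variances are an assumption. Entry requires a Distress Thermometer score of 4 or more, which could narrow the T1 spread, and a T2 SD 20% larger nearly removes the gain at r = 0.65 to 0.74. This stands too. ANCOVA's advantage is moreover a large-sample result: when r is very close to 1, estimating the slope can cost more than it saves.

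Four stronger readings are tempting, and the document does not support them.

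- *The RM-ANOVA is biased by regression to the mean.* It is not, over randomisations. The shift in step 6 is an error conditional on an observed imbalance.
- *The planned main effects mislead about efficacy.* The group main effect has half the treatment effect as its expectation, so it is a diluted test, not an irrelevant one. The time effect has no control, but the plan makes follow-up depend on the interaction.
- *The baseline tests are offered as a correction for imbalance.* The article gives them only as a check on randomisation.
- *Adjustment would rescue the sample size.* Step 5 shows that it would not at 0.51 or 0.58.

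Finally, feasibility is the primary objective and is untouched. But the trial is sized on the efficacy comparison, so its precision still matters.

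**Conclusion.** The point holds as one of lost precision, not of validity. The planned interaction test is sound under randomisation but generally less precise than ANCOVA on T1, and at about 26 per arm it is exposed to chance baseline gaps.

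Under equal T1 and T2 variances and r = 0.65 to 0.74, the ANCOVA variance is 0.83 to 0.87 of the change-score variance, and power at the illustrative effect goes from about 57% to 62–64%. At r = 0.5 it reaches about 68%. With a T2 SD 20% above the T1 SD, and r in the proxy range, it is 57–58%, close to no gain.

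The variance ratio depends on r and k, not on the effect size. The power figures also assume that the cited effects are in SD-of-change units. A reader might take the low power as part of this fault. It belongs to the 26-per-group statement, which needs its own correction.

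**What to change.** Before the arms are compared, amend the section on the primary outcome of the secondary objective as follows:

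- The primary efficacy estimate is the difference between arms in T2 Total Mood Disturbance from an ANCOVA with allocated arm as factor and the T1 score as covariate, reported with its 95% CI.
- This contrast is named as the efficacy test.
- The same model, with each outcome's own T1 score, is used for stress symptoms, mindfulness, spirituality and posttraumatic growth.

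The change-score result can be kept as a supportive analysis, for comparison with the earlier face-to-face trials.

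The cost is a dated amendment made before analysis. It needs no further measurements, because T1 and T2 are in the schedule already, and it runs in SPSS. Recruitment was still open and no between-arm analysis was available when the article was written, so it can be pre-specified. The sample-size statement should be dealt with separately.
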